### Statistical analyses

The primary analysis will follow the intention to treat (ITT) principle; such that, once the participants are randomized they will be analyzed within their randomly assigned group, regardless of compliance with the protocol. As part of the ITT analysis, participants will not be removed from the analysis unless it can be shown that the participant was ineligible prior to randomization (and therefore should never have been included).

#### Primary analysis

We will perform an analysis of covariance (ANCOVA), where the baseline CB&M score serves as the covariate; treatment group as the independent variable, and the follow up CB&M score as the dependent variable. To test our secondary hypothesis about retention, we will repeat this analysis with the retention CB&M score as the dependent variable.

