### Group allocation and data management

Data will be managed using web-based software (EmPower Health Research, http://www.empowerhealthresearch.ca/). Upon registration, the software assigns each participant a unique identification number. Upon screening eligibility, providing signed consent and completion of the baseline assessment, participants will be randomized by the research coordinator using the integrated randomization software, “Integration”. This software protects allocation concealment by ensuring screening is complete and the participant is eligible prior to randomization as well as preventing multiple allocation of the same participant or unjustified removal of participants post-randomization. Participants will be stratified by their (combined leg and foot – affected limb only) CMSA score (≤8 or ≥9) to force a balance between groups in the motor recovery of the leg and foot. The randomization scheme is set up in permuted blocks of 2 and 4 to ensure a similar number of participants between groups and to prevent screening clinicians from guessing the next allocation. All outcome data will be entered into EmPower by the research coordinator, and the accuracy of data entry will be double-checked by a second person who will be blinded to participant group allocation. Research personnel who are to remain blind to group allocation (outcome assessors, data analysts) will not have access to the randomization form when they log into the database to enter data. The data management software contains an audit log that records the user with date and time stamps for all data entries, changes to data and explanations for changes. Data verification and the audit trail ensure high standards of data integrity and validity.

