### Analyses of mechanistic outcomes

We will conduct a similar analysis for all other continuous outcome variables (maximal and self-selected walking speed, EMG parameters, and COM-CP displacement, and ABC score). Because our outcomes are related, we will not adjust our alpha error rate, but rather, look for consistency across outcomes. We will conduct an exploratory analysis to determine whether the variability in walking balance can be explained by the initial participant characteristics (side of lesion, type of stroke, CMSA score, initial ABC score, BBS score). To conduct these analyses, we will use a step-wise least squares method of linear regression where walking balance is the dependent variable, the pre-test measurement is a covariate, and group is an independent variable.

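### Randomisation is stratified by CMSA score but the primary and retention ANCOVAs omit the stratum; if it is prognostic beyond baseline CB&M, standard errors are modestly too large and the tests mildly conservative

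*Protocol article*

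**What the plan says.** Under Group allocation and data management, participants are stratified by the combined leg and foot score of the affected limb: "CMSA score (≤8 or ≥9) to force a balance between groups in the motor recovery of the leg and foot". Within strata, "The randomization scheme is set up in permuted blocks of 2 and 4".

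Under Primary analysis, the protocol names every term of the model: baseline CB&M and treatment group as predictors ("where the baseline CB&M score serves as the covariate; treatment group as the independent variable"), with "the follow up CB&M score as the dependent variable". For the retention hypothesis, "we will repeat this analysis with the retention CB&M score as the dependent variable".

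Under Analyses of mechanistic outcomes, the other outcomes are covered by one sentence: "We will conduct a similar analysis for all other continuous outcome variables". CMSA appears in the analysis plan only there, as one candidate in an exploratory step-wise regression on "initial participant characteristics (side of lesion, type of stroke, CMSA score, initial ABC score, BBS score").

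**The concern.** Blocking within strata makes the two arms nearly equal on the stratum, so the stratum adds almost nothing to the real sampling variance of the treatment difference. An ANCOVA without the stratum does not use this. Any outcome variance that the stratum explains beyond baseline CB&M stays in the residual, and the standard error is computed as if that variance were still random between arms. The reported standard error then exceeds the true one, confidence intervals are wider than the design warrants, and the test rejects a true null less often than the 5% named under Sample size.

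The model is stated term by term, so this concerns what is written and not a detail that an unseen analysis plan might supply.

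**Working it through.** **Inputs from the protocol.** 30 per group; effect size 0.60 SD; pre-post correlation r = 0.75; type I error 5% (sidedness not stated, two-sided assumed); power 80%; two strata; permuted blocks of 2 and 4.

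**Inputs assumed.** The share of outcome variance left after baseline CB&M that the stratum explains (partial R²) is not given, so 0, 5, 10 and 20% are used. The simulation also assumes about half the participants in each stratum and a correlation of 0.3 between baseline CB&M and the latent CMSA score.

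**1. The plan's own figure.** The ANCOVA formula is n per group = 2(1.96 + 0.842)² × (1 − 0.75²) / 0.60² = 2 × 7.85 × 0.4375 / 0.36 = 19.1, so 20 (21 by the noncentral t). The stated 30 is not reproduced. That is a separate matter, but it sets the base here: at 30 per group, power is about 94% by the normal formula and 93% by the noncentral t.

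**2. Standard error.** In SD units, the planned model's standard error is √(0.4375 × 2/30) = 0.171. With the stratum in the model it becomes 0.171 × √(1 − partial R²), so the ratio of omitted to included is 1/√(1 − partial R²).

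**3. Type I error of the planned model.** If balance on the stratum were perfect, the true standard error would be the smaller one. The planned test, with critical value 2.002 on 57 degrees of freedom, in effect uses 2.002 × ratio.

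| Partial R² | SE ratio | Effective critical value | Type I error, analytic |
|---|---|---|---|
| 0 | 1.000 | 2.002 | 5.0% |
| 5% | 1.026 | 2.054 | 4.5% |
| 10% | 1.054 | 2.111 | 3.9% |
| 20% | 1.118 | 2.239 | 2.9% |

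**4. Simulation.** 20,000 trials per setting with n = 60, stratified permuted blocks of 2 and 4, and both models fitted to each trial:

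| Partial R² | Type I error, omitted | Type I error, included | Power, omitted | Power, included |
|---|---|---|---|---|
| 0 | 5.0% | 5.0% | 92.8% | 92.6% |
| 5% | 4.6% | 5.1% | 93.3% | 93.8% |
| 10% | 4.1% | 5.0% | 93.5% | 94.8% |
| 20% | 3.0% | 4.9% | 94.8% | 97.1% |

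At a partial R² of 10%, the planned model reports a mean standard error of 0.1717 against a true sampling SD of 0.1631. With the stratum included, the figures are 0.1628 and 0.1624, so the reported error matches the real one. The simulated type I errors lie slightly above the analytic ones because incomplete blocks leave balance a little short of perfect.

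**5. Power forgone.** The differences in the last two columns are −0.1 (from unrounded rates of 92.75% and 92.63%), 0.5, 1.3 and 2.3 points. A separate simulation of 6,000 trials per setting, under slightly different assumptions, gave 0.5, 1.5 and 2.5 points for 5, 10 and 20%.

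**The case against.** The strongest reply is that the protocol never shows the stratum to be prognostic once baseline CB&M is in the model. It says only that stratification is meant "to force a balance between groups in the motor recovery of the leg and foot", and it leaves to exploration whether CMSA explains walking balance. Baseline CB&M, with an assumed correlation of at least 0.75 with the later score, may already carry much of what leg and foot recovery could predict. The stratum is also a two-level cut of a score that eligibility limits to stages 3 to 6 for each of leg and foot. All of this stands, and it is why the size is a range that starts at zero.

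Four stronger readings are tempting, and the documents do not support them:

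- A reader might infer that the planned test is conservative as a matter of fact. That needs a non-zero partial R², for which no figure is given.
- A reader might infer that the benefit of stratifying is thrown away. In the simulation the planned model's power still rises as the stratum becomes more prognostic, from 92.8% to 94.8%; only part of the gain is forgone.
- A reader might infer that the identical model is fixed for every secondary outcome. Only the retention CB&M analysis explicitly repeats it. For the others the protocol says the analysis will be similar and lists no covariates, and no calculation here covers those outcomes.
- A reader might extend the argument to other baseline variables, such as time since stroke. That is not a stratification factor, so the argument does not reach it.

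It is also fair to say that validity is not at risk: the treatment estimate is unbiased, type I error does not rise above 5%, and power on the stated inputs stays well above 80%. None of this is a reason to keep the model as written, because the remedy costs almost nothing.

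**Conclusion.** The mismatch between the randomisation and the stated model is real, and its consequence is conditional and modest. If the CMSA stratum explains 0 to 20% of the variance left after baseline CB&M, the standard error in the primary analysis is overstated by about 0 to 12%, type I error lies between 5% and about 3%, and about 0 to 2.5 points of power are forgone. In the middle of that range, at 5 to 10%, the figures are about 3 to 5% on the standard error and 3.9 to 4.6% type I error. The direction is certain whenever the stratum is prognostic; the size rests on the assumed partial R², near-equal strata, two-sided testing and the protocol's own r and effect size. The same reasoning holds for retention, with the partial R² at that time point equally unknown.

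**What to change.** State the primary model as follow-up CB&M = treatment group + baseline CB&M + CMSA stratum (≤8 or ≥9, as randomised). Use the same terms for retention CB&M, and say that the stratum is also included in the analyses of the other continuous outcomes. Specify this before outcome data are seen by arm, so that the choice of model cannot look selective.

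The cost is one line of text and one degree of freedom (57 to 56). The variable is already held in the randomisation system. If the stratum turns out not to be prognostic, the loss is negligible: simulated power was 92.6% with the term and 92.8% without it, and the standard error was essentially unchanged.

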### Selection criteria and recruitment of participants

Individuals who have had their first stroke (confirmed by admission CT scan) within the previous 6-months that resulted in unilateral hemiparesis and required in-patient rehabilitation will be invited to participate if they also meet the following inclusion criteria:Sufficient motor control in the paretic lower limb to perform the stepping activities in the FAST program: Chedoke McMaster Stroke Assessment (CMSA) [24] leg and foot scored as stages 3–6 (stage 7 consider ‘normal’). CMSA leg and foot scores reflect the presence and severity of motor impairment following stroke, and they are used clinically to evaluate motor recovery [25].Standing balance ability necessary to participate safely in the FAST program: Berg Balance Score (BBS) ≥ 30/56 [26]. The BBS has established validity and excellent reliability in for assessing functional balance in people following stroke [27].Cognitive capacity to provide informed consent: Mini-Mental Status Examination score ≥ 24/30 [28].

We will exclude individuals with:Bilateral stroke or a history of previous stroke(s) for which inpatient rehabilitation was received.Severe co-morbidities likely to dominate the pattern of care (e.g. metastatic disease, severe congestive heart failure, etc.), co-existing peripheral neuropathies or vestibular disorders likely to independently have a negative impact on balance, and severe musculoskeletal problems or pain; as these conditions would be likely to impede participation in the study interventions.Global aphasia, receptive aphasia or language barriers who do not have someone to assist them in translating information, as these individuals would have difficulty providing informed consent or understanding exercise instructions.

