### Outcome assessment and data collection

A summary of the measures to be collected at four time points (enrolment, baseline, follow up and retention) is provided in Table 2. The research coordinator will administer and record the MMSE to establish eligibility. The other clinical measures used to establish eligibility (BBS, CMSA leg and foot scores) and descriptive data including general demographic information (gender, age, hand dominance), stroke-specific information (date of stroke, type, side and location of stroke), co-morbidities and past medical history will be collected from charted information. Primary and secondary outcome measures and associated information recorded at Baseline, Follow up and Retention assessments will be conducted at University of British Columbia by the same blinded physiotherapy assessor. Participants will be asked to wear the same shoes for all assessment sessions.

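### The primary ANCOVA adjusts only for baseline CB&M; prespecifying time since stroke, already derivable from collected data, could gain precision at almost no cost

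*Protocol article*

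**What the plan says.** - **Primary model (Primary analysis).** The ANCOVA is defined as one "where the baseline CB&M score serves as the covariate; treatment group as the independent variable", with follow-up CB&M as the outcome. It is repeated with the retention score as the dependent variable. No other covariate is named.
- **Eligibility (Selection criteria and recruitment of participants).** Participants have had a first stroke "within the previous 6-months that resulted in unilateral hemiparesis and required in-patient rehabilitation".
- **Data collected (Outcome assessment and data collection, and Table 2).** The stroke-specific items taken from the chart at enrolment include "date of stroke, type, side and location of stroke". Randomisation follows the baseline assessment, so days since stroke at baseline is known beforehand.
- **Stratification (Group allocation and data management).** The one factor named is motor recovery: "Participants will be stratified by their (combined leg and foot – affected limb only) CMSA score (≤8 or ≥9"). It is not in the stated primary model either.
- **Exploratory regression (Analyses of mechanistic outcomes).** The initial characteristics listed are "side of lesion, type of stroke, CMSA score, initial ABC score, BBS score". Time since stroke is not among them.

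**The concern.** Baseline CB&M records a participant's level at entry. It does not record how quickly that person is still changing. Entry may fall anywhere within six months of stroke, and the primary outcome is measured after 6 to 10 weeks of treatment. Two people with the same baseline score but different times since stroke might therefore be expected to reach different follow-up scores. If so, that difference sits in the residual variance of the planned model, and a covariate already in the database could remove part of it.

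What is at stake is the standard error of the FAST effect at follow-up and retention. The validity of the comparison is not in question. The choice also has to be made in advance, because a covariate added after the data are seen would be open to challenge.

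**Working it through.** **Inputs from the Sample size section:** effect size d = 0.60, taken as SD units of CB&M; pre-post association of at least 0.75, read as a correlation r; type I error 5%; power 80%; 30 per group. Sidedness is not stated, so two-sided is assumed.

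**Input the protocol does not give:** the partial R² of time since stroke for follow-up CB&M, given baseline CB&M. It is varied from 0 to 0.20.

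**1. The plan's own figure.** n per group = 2(z₀.₉₇₅ + z₀.₈₀)²(1 − r²)/d² = 2 × (1.960 + 0.842)² × 0.4375/0.36 = 19.1, so 20 per group (21 with the t distribution). The stated 30 does not follow from these inputs. At 80% power it would correspond to r of about 0.56. That is a separate matter, but it means two starting points should be shown.

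**2. Power of the planned model at 30 per group, r = 0.75.** Residual variance is 1 − 0.75² = 0.4375. The standard error is √(0.4375 × 2/30) = 0.1708 and the noncentrality is 0.60/0.1708 = 3.513. With 57 degrees of freedom, power is 93.2%.

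**3. Adding time since stroke.** The residual variance becomes 0.4375 × (1 − partial R²), with 56 degrees of freedom. Allowing for the extra estimated coefficient, the net variance ratio against the planned model is (1 − partial R²) × (1 + 1/56). The equivalent number of participants is 60 divided by that ratio.

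| Partial R² (assumed) | Net variance ratio | Equivalent N | Power, r = 0.75 | Power, r ≈ 0.56 |
|---|---|---|---|---|
| Planned model | 1 | 60 | 93.2% | 78.9% |
| 0 | 1.018 | 59 | 93.2% | 78.9% |
| 0.02 | 0.9975 | 60 | 93.7% | 79.7% |
| 0.05 | 0.967 | 62 | 94.3% | 80.9% |
| 0.10 | 0.916 | 65 | 95.3% | 82.9% |
| 0.20 | 0.814 | 74 | 97.1% | 87.0% |

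The power columns charge the extra term one degree of freedom only. Charging the 1/56 variance cost as well lowers them slightly: at partial R² = 0 and r = 0.75 the noncentrality is 3.513/√1.018 = 3.482 and power is 92.8%.

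**4. Break-even.** Setting (1 − R²)(57/56) = 1 gives R² = 1/57, or about 1.8%. Below that the covariate costs slightly more than it returns.

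**5. Chance imbalance.** The standard error of the between-arm difference in time since stroke is √(2/30) = 0.26 SD. With residual SD √0.4375 = 0.66, an imbalance of that size moves the unadjusted estimate by 0.26 × 0.66 × √0.05 = 0.04 SD at partial R² 0.05, and by 0.26 × 0.66 × √0.20 = 0.08 SD at 0.20. The planned effect is 0.60 SD.

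**The case against.** The strongest reply is that nothing here is wrong. A baseline-adjusted ANCOVA in a randomised trial is unbiased and holds its type I error whether or not a further prognostic covariate is included. It is also the model on which the sample size was planned. That stands in full.

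The second reply is that the premise is undocumented. No section says that time since stroke predicts follow-up CB&M once baseline CB&M is known. Participants are approached by the inpatient physiotherapist and treated after discharge, so time since stroke is tied to length of rehabilitation stay. The actual spread may be narrower than the six-month limit suggests. Part of what the variable carries may be severity, which baseline CB&M and the CMSA stratification already address in part. This also stands, and it is why the table starts at zero.

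A reader might infer that recovery-related variance certainly remains in the error term. The protocol does not support that without a partial R². A reader might also infer that a chance imbalance in time since stroke distorts the FAST effect. Such imbalance is part of the sampling variation that the standard error already covers, and a typical one is small against 0.60 SD.

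What survives is the asymmetry: the worst case costs about 2% of variance, and a modest association returns more than that.

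**Conclusion.** The point holds as an efficiency improvement. The plan fixes a primary model with a single covariate and leaves unused a baseline value that it collects for everyone and that could bear on the outcome.

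On the planned correlation of 0.75, the gain in power ranges from nil to about 4 points (93.2% to 97.1%) as partial R² goes from 0 to 0.20. If true power at 30 per group is nearer 80%, the gain is up to about 8 points (78.9% to 87.0%). The variance of the treatment estimate changes by between +1.8% and −18.6%. These figures rest on a two-sided 5% test, 30 completers per group, d = 0.60 in SD units and an assumed partial R². The trial's planned 80% power does not depend on this covariate.

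**What to change.** In the Primary analysis section, prespecify days since stroke at the baseline assessment as a covariate beside baseline CB&M, in one stated functional form (for example log days). Use the same model for the retention analysis. Preferably include the CMSA stratum used in randomisation (≤8 or ≥9) as well, since it is a design factor that the stated model also leaves out. Fix the choice before any unblinding.

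The cost is a sentence of text and one degree of freedom per added term. For time since stroke that is about 2% of variance if it turns out to carry no information. No new data are needed.

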The primary objective of this assessor-blinded, parallel design, randomized controlled trial is to investigate the effectiveness of an outpatient FAST program commenced within the first six months following stroke compared to an active control intervention of conventional outpatient physiotherapy (active control) that includes no targeted fast movement training for improving walking balance. As many people fall in the first few months after discharge from inpatient rehabilitation, this was thought to be an important window for this balance intervention [19]. The primary hypothesis is that improvements in walking balance (as measured with the Community Balance and Mobility Scale, CB&M [20,21]) will be larger following 12 sessions of FAST intervention compared to 12 sessions of active control intervention. The secondary hypothesis is that CB&M scores will continue to be higher in the FAST group compared to the active control group one month following the intervention. Another aim of this study is to explore potential mechanisms associated with improvements in walking balance including; improvements in walking speed, balance self-efficacy, ability to respond to internal and external perturbations to balance and associated changes in postural muscle activation. Our *mechanistic hypotheses* are that compared to the active control intervention; the FAST retraining will result in:Increased fast and self-selected natural walking speed (gait assessment);Reduced postural sway (balance perturbation assessment);Improved timing and amplitude of muscle activation (EMG onset timing, burst area and slope) during balance perturbations and gait;Increased balance self-efficacy (using Activities-specific Balance Confidence (ABC) scale).

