## Methods

### Study design

The study is a single-blind, parallel design, randomized controlled trial, with the assessor blinded to the group allocation of the participants (Figure 1). The participants cannot be blinded to the interventions that they receive, though they will not be aware of the details of the other study arm. Eligible participants who provide written consent will be randomly assigned, to the FAST or active control group. Interventions will be received following discharge from inpatient rehabilitation in the outpatient departments of two hospitals in the Greater Vancouver area; Holy Family and Lion’s Gate Hospitals. Outcome measurements will be evaluated at the University of British Columbia at three time points (Figure 1): 1) baseline (prior to the first intervention session), 2) follow up (within one week of the 12th intervention session), 3) and retention (one month following the 12th intervention session) by the same blinded assessor. This study was approved by the University of British Columbia Human Research Ethics Committee. This protocol is reported in accordance with SPIRIT guidelines [22,23].

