**Table 2 Tab2:** **Measures collected at enrolment and the three assessment time points**

	**Time 1: Study enrolment**	**Time 2: Baseline assessment**	**Time 3: Follow up assessment**	**Time 4: Retention assessment**
Demographic information	✓			
Stroke specific information	✓			
Medical information	✓			
Mini-mental Status Exam	✓			
Chedoke-McMaster Stroke Assessment leg & foot score	✓	✓	✓	✓
Berg Balance Scale	✓	✓	✓	✓
Community Balance and Mobility Scale		✓	✓	✓
Activities-specific Balance Confidence questionnaire		✓	✓	✓
10 Metre Walk Test (fast walking speed)		✓	✓	✓
Biodex – maximum voluntary contraction EMG		✓	✓	✓
Self-selected walking speed		✓	✓	✓
Gait – kinematic, kinetic and EMG parameters		✓	✓	✓
Physiological Balance Test – Postural stress test (external perturbations)		✓	✓	✓
Physiological Balance Test – Arm raise task (internal perturbations)		✓	✓	✓
Physiological Balance Test – Stepping Reactions (internal perturbations)		✓	✓	✓
Helpfulness of treatment received in improving balance			✓	✓

Reasons for missing outcome assessments or treatment sessions will be recorded. Where possible, outcomes will still be collected at planned time points, even if the treatment sessions were not completed, in accordance with intention-to-treat analyses.

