### Sample size

Data from our published study of a similar FAST training protocol in individuals with chronic stroke showed an effect size of 1.9 SD with the intervention group and a pooled standard deviation of 7.45 for the pre and post CB&M score (primary outcome measure) [18]. Using our pilot data and a sample size equation suitable for our planned between-group comparisons using an analysis of covariance (ANCOVA); where we estimated that the magnitude of the association between the pre- and the post-intervention CB&M scores would be at least 0.75 and that a conservative estimate of effect size would be 0.60, we estimate that 30 participants per group (60 participants in total) are required to maintain a Type I error rate of 5% and 80% power to detect a difference between intervention groups. Therefore, recruitment will continue until a total of 30 participants in each group have completed the follow up assessment.

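### The retention ANCOVA leaves out the follow-up CB&M: harmless if everyone returns at one month, slightly less precise and open to a specific bias if participants are lost after follow-up

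*Protocol article*

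**What the plan says.** The Primary analysis section sets the model for the follow-up visit: "We will perform an analysis of covariance (ANCOVA), where the baseline CB&M score serves as the covariate", with treatment group as the independent variable and follow-up CB&M as the outcome. For the secondary hypothesis, "we will repeat this analysis with the retention CB&M score as the dependent variable". The follow-up CB&M has no place in that second model.

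The hypothesis itself is in the Background: "CB&M scores will continue to be higher in the FAST group compared to the active control group one month following the intervention". CB&M is measured at baseline, at follow-up within a week of session 12, and at "retention (one month following the 12th intervention session) by the same blinded assessor" (Study design).

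Two other statements bear on who contributes a retention score. The Sample size section continues recruitment until 30 per group have completed follow-up and has no matching rule for retention. The text under Table 2 allows for missed visits: "Reasons for missing outcome assessments or treatment sessions will be recorded", with outcomes collected where possible even when treatment was not completed.

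**The concern.** A participant seen at follow-up but not at one month already has a CB&M score, taken about a month before the missing one. That score is likely to be the best available predictor of the missing value. A stand-alone ANCOVA of retention on baseline and group makes no use of it. Two things are at stake if participants are lost in the last month:

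- **Precision.** Information already collected is left unused.
- **Bias.** If those who stay away did unusually well in one arm and unusually badly in the other, the one-month difference among returners is distorted, and baseline CB&M cannot correct for it.

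The test affected is the only one the protocol labels its secondary hypothesis.

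**Working it through.** **Inputs from the protocol (Sample size).** "a conservative estimate of effect size would be 0.60"; "the magnitude of the association between the pre- and the post-intervention CB&M scores would be at least 0.75"; 30 per group; the numbers "are required to maintain a Type I error rate of 5% and 80% power to detect a difference between intervention groups". Two-sided testing is assumed, since sidedness is not stated.

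**Inputs assumed.** The protocol gives no loss rate between follow-up and retention and no correlation between those two scores. Loss of 10% to 30% and a correlation ρ of 0.80 to 0.95 are used. The effect (0.60 SD) and the baseline correlation (0.75) are assumed to hold at retention too.

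**The plan's own figure.** For ANCOVA, n per group = 2(1.96 + 0.84)² × (1 − 0.75²) / 0.60² = 2 × 7.85 × 0.4375 / 0.36 ≈ 19.1, so 20 (21 with the t distribution). The stated 30 is not reproduced. On these inputs 30 per group gives about 94% power. That is a separate matter, but it means there is slack at retention.

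**Power at retention after loss.** SE = √(2 × 0.4375 / m), with m per arm:

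| m per arm | SE (SD units) | 0.60/SE − 1.96 | Power |
|---|---|---|---|
| 27 | 0.180 | 1.37 | 92% |
| 24 | 0.191 | 1.18 | 88% |
| 21 | 0.204 | 0.98 | 84% |

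Lost precision alone does not take the test below 80%.

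**Gain from a joint model, loss at random.** The partial correlation of follow-up and retention given baseline is (ρ − 0.75²)/(1 − 0.75²). With a fraction p lost, the variance of the retention contrast falls by about p times its square.

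| ρ | Partial correlation | Squared | Fall at 10% | Fall at 20% |
|---|---|---|---|---|
| 0.80 | 0.2375/0.4375 = 0.543 | 0.295 | 2.9% | 5.9% |
| 0.90 | 0.3375/0.4375 = 0.771 | 0.595 | 6.0% | 11.9% |
| 0.95 | 0.3875/0.4375 = 0.886 | 0.784 | 7.8% | 15.7% |

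Simulation (6,000 trials per scenario, 30 per arm) agrees: 2-9% at 10% loss, 6-16% at 20%, and 1-4% at 5%. With no loss the two estimates coincide (largest difference 3 × 10⁻¹⁵ over 500 trials).

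**Bias, true difference 0.60 SD, ρ = 0.90.** Selective loss has a log-odds slope of 1 per SD.

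| Loss pattern | Loss | Planned ANCOVA | Joint model |
|---|---|---|---|
| Unequal rates only | 25% v 5% | 0.601 | not needed |
| Depends on baseline, opposite by arm | about 15% | 0.604 | not needed |
| Depends on follow-up score, same direction in both arms | 13%, 24% | 0.598, 0.597 | 0.60 |
| Depends on follow-up score, FAST arm only | 10-24% | 0.640 (lower loss), 0.670 (higher loss) | 0.60 |
| Depends on follow-up score, opposite by arm, inflating | 13%, 24% | 0.683, 0.751 | 0.60 |
| Same, sign reversed | 13%, 24% | 0.518, 0.452 | 0.60 |
| Depends on response given baseline, opposite by arm | 13%, 24% | 0.476, 0.390 | 0.60 |

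The opposite-selection rows give a bias of 0.08 to 0.21 SD (0.60 − 0.518 = 0.08; 0.60 − 0.390 = 0.21). Reversing the sign in the last row gives a bias of the same size upwards. At the protocol's pooled SD of 7.45 this is 0.6 to 1.6 CB&M points (0.08 × 7.45; 0.21 × 7.45), or 13% to 35% of the planned effect.

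**The case against.** The strongest reply has three parts.

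- **The planned ANCOVA answers the stated question.** The hypothesis is a between-group difference at one month, and the retention ANCOVA estimates exactly that. This stands. A reader might infer that the plan cannot show whether the benefit lasted, or that it will judge persistence by setting one p-value against another. The protocol supports neither: it proposes no such comparison and does not pose change between visits as a hypothesis. Nor would disagreement between the two tests when nobody is lost be an argument for the joint model, which gives the same estimates then.
- **No complete-case rule is stated.** Handling of missing scores is commonly left to an analysis plan, which is not shown. The Statistical analyses section, on the intention-to-treat principle, keeps randomized participants in the analysis. The same ANCOVA after imputation using follow-up CB&M would recover the lost information. This also stands, so the absence of a missing-data rule is not the point here. The point is that the model actually named has no term through which the follow-up score can contribute.
- **The bias needs a particular pattern.** A reader might infer bias whenever losses differ by arm. The table shows otherwise: unequal rates, or loss explained by baseline, leave the ANCOVA unbiased. The larger figures come from deliberately strong, opposite selection.

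**Conclusion.** The point holds as a modest refinement of a secondary analysis. The planned test is valid, and with full attendance at one month nothing changes. If participants are lost after follow-up, the cost in precision is small (2-9% of variance at 10% loss, 6-16% at 20%), and power on the plan's own inputs stays above 80% even at 30% loss. Bias is the more serious possibility but is conditional. It requires loss that depends on the follow-up score, given baseline, differently by arm. It is then about 0.08-0.21 SD in either direction at 13-24% loss under strong opposite selection, so it could hide a retained effect or exaggerate one.

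These sizes rest on assumed loss rates, an assumed follow-up to retention correlation and an assumed selection strength. They also treat those without a retention score as left out of the ANCOVA.

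**What to change.** Keep the planned ANCOVA as the primary analysis at follow-up. Keeping it separate means that anyone who misses follow-up but attends retention cannot alter the primary estimate.

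For the secondary hypothesis, take the one-month contrast from a likelihood-based repeated-measures model of follow-up and retention CB&M, with group-by-visit and baseline-by-visit terms and an unstructured covariance. Do not add follow-up CB&M as a covariate to the retention ANCOVA: it is measured after randomization, and adjusting for it would remove much of the effect being estimated.

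Report the change in the group difference from follow-up to retention with its 95% confidence interval, labelled descriptive. The one-month contrast remains the test.

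The cost is a paragraph of analysis wording and slightly more analysis work, with no new data or visits. The model assumes data missing at random, so it does not protect against loss that depends on the unseen retention score.
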